## Trial design {8}

Due to the present study’s focus on measuring undue influence, which may not be consciously perceived by patients and is uniquely vulnerable to bias, the described trial relies on an element of deception (similar to psychological studies of phenomena in which nondeceptive procedures are not feasible) [27]. We propose a prospective single-blinded randomized controlled non-inferiority trial (the ‘Consent Study’) examining the voluntariness of patient consent to participate in an anesthesia research trial (the ‘Dummy Trial’; a fictitious low-risk randomized clinical anesthesia research trial) at Women’s College Hospital (WCH) when such consent is obtained (a) prior to the day of surgery compared to (b) on the same day as surgery compared to. The study design is illustrated as a flow diagram (provided in Fig. 1), and presented here in the form of a SPIRIT Figure.

**Fig. 1 Fig1:**
[figure not shown]
Study design flow diagram

**Table Tabb:**
[figure not shown]

*ACL* anterior cruciate ligament, *PAC* preadmission clinic

For the purposes of the Consent Study, all patients will be recruited at one of these two timepoints to participate in the Dummy Trial, a fictitious low-risk randomized clinical anesthesia research trial entitled “The AADDCToR Trial: A Randomized-Controlled Comparison of the Analgesic Effects Following Anterior Cruciate Ligament Repair.”, for which a trial protocol has already been approved by our local REB (REB# 2018-0164-B, 2019-Mar-01) and registered [28], but not yet completed. The Dummy Trial purports to compare the efficacy of adjuncts (dexamethasone and/or dexmedetomidine) combined with local anesthetics in adductor canal blocks for post-operative analgesia.

To preserve the deception required for naturalistic observation, the present trial was pre-registered in advance of participant recruitment and published under an embargo to prevent eligible participants from prematurely unblinding themselves to the true nature of the study.

## Methods: participants, interventions, and outcomes

### Study setting {9}

This is a single-center study undertaken at WCH, an academic hospital in Toronto, Canada.

### Eligibility criteria {10}

Patients scheduled to undergo ambulatory anterior cruciate ligament (ACL) repair facilitated by general anesthetic with an adductor canal block (the anesthetic standard of care for this operation) at WCH will be eligible to participate in the Consent Study. As per our standard practice, all patients undergoing ACL repair will be assessed 1–2 weeks prior in our PAC. The specific eligibility criteria will be:

Inclusion criteriaPresentation at the WCH PAC for outpatient ACL repair surgery with general anesthesia and an adductor canal block.

Exclusion criteriaInability to provide informed consent.◦ All patients seen in the PAC and on the surgical date for this elective procedure have provided informed consent to undergo their surgery, and so it is presumed that they will have capacity to consent to the present study without former assessment. However, any patient in which there is an indication that they cannot consent for themselves in the surgical consent process would not be approached for this study.

### Who will take informed consent? {26a}

Eligible participants will be approached by a clinical research coordinator with an invitation to participate in the Dummy Trial. Recruitment will follow standard processes, using an informed consent package identical to that devised for the AADDCToR Trial (with only the dates and investigator information updated).

Additionally, in order to measure the extent of voluntariness related to the Dummy Trial consent process, all patients recruited at either timepoint will be asked to consent to completing a concise questionnaire and debrief relating to their peri-operative experience (“Feedback Session”), after their surgery. Because the nature of the Consent Study will be explained in the Feedback Session, patients will not be offered an opportunity to consent to only the Dummy Trial and not the Feedback Session. Any patients who choose not to provide consent for participation in the Dummy Trial and Feedback Session will receive the standard of care (identical to those who consent for participation). However, because we believe that patients who elect not to consent to the Dummy Trial may be able to offer critical insights about perceptions of coercion or undue influence in invitations to participate in clinical research, these patients will be approached once more in the post-operative setting before discharge from hospital with a final invitation to participate in the Feedback Session.

### Additional consent provisions for collection and use of participant data and biological specimens {26b}

On the consent form, participants will be asked if they agree to the use of their data should they choose to withdraw from the trial. They will also have the opportunity to reaffirm their consent for this data to be analyzed, following the post-operative Feedback Session. Furthermore, participants will be asked to grant permission for the research team to share relevant data with people from the University taking part in this research and/or from regulatory authorities, where relevant. This trial does not involve collecting biological specimens for storage.

## Interventions

### Explanation for the choice of comparators {6b}

Patients randomized to the control group will be approached and invited to participate in the Dummy Trial at the time of their PAC visit. As per our standard practice for peri-operative trial recruitment, informed consent for participation in the Dummy Trial will be obtained from patients at the time of their PAC visit prior to the day of surgery.

### Intervention description {11a}

Patients randomized to the intervention group will complete their PAC visit without recruitment to any research trials. Patients in this group will be approached and invited to participate in the Dummy Trial pre-operatively, on the same day as surgery.

The Dummy Trial purports to compare the efficacy of adjuncts (dexamethasone and/or dexmedetomidine) combined with local anesthetics in adductor canal blocks for post-operative analgesia. However, all patients will receive the standard of care (an adductor canal block placed in a proximal location followed by a general anesthetic) with no true comparison of nerve block adjunct efficacy, regardless of their decision to participate in the Dummy Trial.

The Feedback Session will be an individualized session conducted post-operatively for all patients who consent to participate in the Dummy Trial, prior to discharge from hospital. The Feedback Session will be comprised of a pen-and-paper written questionnaire (modified by our research team from the Iowa Coercion Questionnaire and Coercion Assessment Scale) [25, 26]. This questionnaire comprises demographic information and items probing participants’ perception of the consent process which they undertook, and is provided as Additional file 1. If any specific accommodation or assistance is required to complete the pen-and-paper questionnaire, our study team will strive to provide these. The written questionnaire, which we anticipate will take between 5 and 10 min, will be followed by a scripted 10-min verbal debrief prior to discharge from hospital on the day of surgery, which serves to inform participants of the true nature and intent of the Consent Study and Dummy Trial. At this time, patients will have an opportunity to reconfirm consent, in keeping with Article 3.7A of the TCPS [1]. Patients who initially declined to participate in the Dummy Trial, but agree to participate in the Feedback Session, will be provided the same questionnaire and verbal debrief to assess their perceptions of the consent process and explain the intention of the study they had been invited to participate in.

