### Outcomes {12}

The primary outcome is participants’ score on the post-operative questionnaire, which is designed to reflect perceptions of undue influence to consent to participation in the Dummy Trial.

Secondary outcomes include patients’ perceptions of how informed they were with respect to the consent provided to participate in the Dummy Trial, and rate of enrollment in the Dummy Trial. In addition, an exploratory secondary analysis is planned to examine the potential relationships between participants’ demographic variables and the primary outcome.

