### Sample size {14}

Based on our hypothesis that voluntariness will be similar between the two study groups, this trial is powered as a non-inferiority RCT. Drawing on data from previous reports validating the questionnaires adapted for this trial [26], we calculate that a sample size of 102 patients (51 in each group) will be needed to assess that the intervention group is non-inferior to the control group with 80% power (alpha = 0.05), with respect to the main outcome defined as the average questionnaire score (continuous measure ranging from 1 to 4), using a two-sample equal-variance *t*-test. We assumed a non-inferiority margin of − 0.3 and a common standard deviation of 0.6 (assumed to be a 5th of the average score range). In order to account for the assumed at most 10% of patients who would decline to participate in this Feedback Session, having not enrolled in the Dummy Trial, the randomization sample size will be 114 patients (57 in each group). The sample size was computed using PASS 2023, version 23.0.2.

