## Statistical methods

### Statistical methods for primary and secondary outcomes {20a}

We will use descriptive statistics to summarize demographic information and baseline characteristics. We will reorder item responses from least to greatest perception of coercion (e.g., “someone tried to force me to be in this study” would be unchanged, with 1 = “not at all”, while “I chose to be in this study” would flip such that 1 represents “very much so) to calculate overall undue influence scores for each discrete section and the questionnaire as a whole. We will perform chi-square tests for ordinal responses to each item on the study questionnaires. We will also define the total average score for each questionnaire as the sum of individual item answers divided by the total questions answered, resulting in a continuous measure ranging from 1 to 4. To compare these average scores in patients approached for research consent prior to or on the day of surgery, we will use t-tests or non-parametric Wilcoxon tests.

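### Decliners of the Dummy Trial are scored with the same reverse-coded, enrolment-worded items as enrollers, so the primary score partly measures enrolment status

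*Protocol article*

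**What the plan says.** Intervention description {11a} gives responding decliners the enrollers' instrument: "Patients who initially declined to participate in the Dummy Trial, but agree to participate in the Feedback Session, will be provided the same questionnaire". The section on who takes consent {26a} has the team approach decliners again before discharge to obtain these responses.

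Statistical methods {20a} sets one scoring direction for all respondents: "We will reorder item responses from least to greatest perception of coercion". Its example of a flipped item is "I chose to be in this study” would flip such that 1 represents “very much so". On a 1 to 4 scale, the opposite answer, 'not at all', then becomes 4. The total score is "the sum of individual item answers divided by the total questions answered, resulting in a continuous measure ranging from 1 to 4". The comparison covers everyone invited: "To compare these average scores in patients approached for research consent prior to or on the day of surgery".

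Sample size {14} allows for losing only patients who "decline to participate in this Feedback Session, having not enrolled in the Dummy Trial". A decliner who does attend therefore counts among the 102 evaluable patients. Outcomes {12} describes the primary score as "designed to reflect perceptions of undue influence to consent to participation in the Dummy Trial" and lists the Dummy Trial enrolment rate as a secondary outcome. The section on missing data {20c} averages over completed questions only. The article describes no decliner version of the form, no exclusion of items and no separate scoring.

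**The concern.** For an enroller, a low rating on an item about having chosen to take part may signal pressure. For someone who freely said no, the same low rating is simply a true statement about not being in the study. The reverse-coding rule treats the two alike, so for decliners the item records the decision and not how freely it was made. If the decliner leaves the item blank, the two kinds of respondent are scored on different content.

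The trial compares arms that differ in when consent is sought, and it measures enrolment as an outcome of that timing. Any difference in decliner share passes straight into the primary contrast. The awkward case is the one the trial exists to detect. If same-day pressure makes more people enrol, the same-day arm has fewer decliners, collects fewer of these artificial 4s, and finds non-inferiority easier to show. If same-day patients refuse more often, a fully voluntary arm looks coerced.

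**Working it through.** **Inputs from the protocol.** Margin 0.3 in absolute value, SD 0.6, alpha 0.05, power 80%, equal-variance t-test, 51 per arm evaluable, 10% allowance (Sample size {14}); score range 1 to 4, higher meaning more undue influence (Statistical methods {20a}).

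**Assumptions, not in the protocol.** The form has k = 10 to 20 items, of which r = 1 to 3 are enrolment-worded and reverse-coded. The decliner share among respondents differs by 20 percentage points between arms. Every decliner answers these items literally and so scores 4 where a freely consenting enroller scores 1.

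**Reproducing the stated sample size.** SE = 0.6 × √(2/51) = 0.1188, with df = 100. At one-sided 0.05 the noncentral t gives power 80.6% with 51 per arm and 79.9% with 50, so 51 per arm (102) is confirmed. 102/0.9 = 113.3, rounded up to 114. One-sided 0.025 would need 64 per arm, so the stated alpha is one-sided 0.05.

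**Size of the artefact.** Each affected item adds 4 − 1 = 3 points to a decliner's sum, and so 3/k to the average. With r items the shift per decliner is 3r/k. The shift in the arm difference is

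bias = (difference in decliner share) × 3r/k.

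False non-inferiority is the chance of declaring non-inferiority at a true difference of 0.3 when the bias favours the same-day arm. Power is at a true difference of 0 with the bias the other way. SD is held at 0.6.

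| Items r of k | Bias | Share of margin | False non-inferiority | Power, opposite bias |
|---|---|---|---|---|
| none | 0 | 0% | 5% | 81% |
| 1 of 20 | 0.2 × 3 × 1/20 = 0.03 | 10% | 8% | 73% |
| 1 of 10 | 0.2 × 3 × 1/10 = 0.06 | 20% | 13% | 64% |
| 3 of 20 | 0.2 × 3 × 3/20 = 0.09 | 30% | 19% | 54% |
| 3 of 10 | 0.2 × 3 × 3/10 = 0.18 | 60% | 44% | 26% |

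**Smaller gap.** A 10-point difference with 1 of 20 items gives a bias of 0.1 × 3/20 = 0.015, false non-inferiority of 6.4% and power of 77%.

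**Effect on the SD.** Mixing decliners and enrollers also widens the score distribution. With 3 of 10 items and decliner shares of 10% and 30%, the SD is about 0.69. False non-inferiority is then 37% rather than 44%, and power 22% rather than 26%. With equal decline rates the bias is zero and only this widening remains: with 20% of items affected and 30% decliners in both arms, the SD is 0.66 and power 74%.

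**The case against.** The strongest reply is that the instrument is in Additional file 1, which is not at hand. The flipped item appears in the protocol only as an example. The form may carry a not-applicable option, a skip instruction or neutral wording elsewhere. A decliner who leaves the item blank avoids the 4 altogether. This stands as a limit on the size and on how sure one can be of any individual's answer. It does not remove the point, because the protocol names at least one affected item, gives the form to decliners and states one rule for all. Skipping exchanges the artefact for unequal item sets.

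A second reply is that the hypothesis in Objectives {7} speaks of patients from whom consent was obtained, so decliners might not belong in the primary analysis, and exact analysis sets are often left to a statistical analysis plan. The sample-size allowance and the comparison of all patients approached point the other way, and they are the more specific statements.

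Three stronger readings are tempting and are not supported:

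- A reader might infer that a free refusal scores as maximum coercion overall. It does so only on the enrolment-worded reversed items. The same patient would still score 1 on the item about someone trying to force them.
- A reader might infer that enrolment is expected to differ by arm. Outcomes {12} only lists it as an outcome, and nothing in the protocol predicts a difference.
- A reader might take the 44% as the likely error rate. It is the extreme corner of the assumed range, and every figure in the table assumes that all decliners answer literally.

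**Conclusion.** The point holds as a defect in how the primary score is defined. The same form for decliners, their inclusion in the comparison and a single reverse-coding rule together make the score depend partly on enrolment status. Whether this biases the result depends on whether decliner shares differ between arms, which the protocol neither predicts nor rules out. The bias can run in either direction.

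Under the stated assumptions it is at most 0.03 to 0.18 points against a margin of 0.3. That range runs from a modest loss of error control to a serious one, and the actual item wording would narrow it. With one such item on a long form and similar decline rates, the effect is small. Because the affected quantity is the primary endpoint and the remedy is cheap, it should be settled before data lock.

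**What to change.** Preferred: reword the participation-specific items so that they carry the same meaning whatever the patient decided, for example 'I freely chose whether or not to be in this study', and use that wording for everyone.

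If the form cannot change: define the primary score in Statistical methods {20a}, before data lock, from items that do not presuppose enrolment, with the same item set for enrollers and decliners.

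Do not simply leave these items unreversed for decliners. 'Not at all' would then score 1, and every refuser answering literally would be coded as uncoerced on those items, including any who felt pressed to refuse.

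Results by enrolment decision may be reported as a descriptive sensitivity analysis only. The decision is made after randomisation and may itself depend on timing, so those subgroups are not randomised comparisons.

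Cost: an ethics board amendment for new wording, or a scoring rule alone, and slightly less comparability with the two source instruments, which the team has already modified.

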### Criteria for discontinuing or modifying allocated interventions {11b}

Not applicable: this trial does not account for the discontinuation or modification of allocated interventions, as allocation precedes patient recruitment.

### Strategies to improve adherence to interventions {11c}

Not applicable: adherence to interventions is not dependent on participants, in the context of this trial.

### Relevant concomitant care permitted or prohibited during the trial {11d}

All participants in this trial, regardless of group allocation, will receive the standard of care.

### Provisions for post-trial care {30}

No harms are anticipated to arise in the course of this trial. In order to minimize the possibility of patient distress (e.g., after revealing the deceptive nature of the Dummy Trial), our debriefing meetings will contain a thorough explanation of the rationale for deception to measure the psychological construct of voluntariness in the Consent Study. Nevertheless, our debriefing team will actively monitor for any adverse events such as patient distress, and inquire about patients’ emotional state at the end of the debriefing session. Any acutely distressed patient will be referred to or directly provided support services such as counseling; several members of our study team are professionally trained to manage distress and provide emotional support should this need arise. Any instances of patient distress will be carefully documented as an adverse event, and included in the study team’s regular review. This information will be used to assess whether any trial protocol adjustments can be made to minimize discomfort without compromising scientific integrity, or whether prematurely stopping the study should be considered.

### Outcomes {12}

The primary outcome is participants’ score on the post-operative questionnaire, which is designed to reflect perceptions of undue influence to consent to participation in the Dummy Trial.

Secondary outcomes include patients’ perceptions of how informed they were with respect to the consent provided to participate in the Dummy Trial, and rate of enrollment in the Dummy Trial. In addition, an exploratory secondary analysis is planned to examine the potential relationships between participants’ demographic variables and the primary outcome.

### Participant timeline {13}

Participants will be randomized into groups invited to participate in the Dummy Trial either in the PAC (approximately 1–2 weeks in advance of surgery) or on the day of surgery. Post-operatively, prior to discharge from hospital, they will be approached to complete the Feedback Session including completion of the study questionnaire and debriefing. A flow diagram illustrating the study’s design is provided in Fig. 1. There will be no later follow-up assessments.

### Sample size {14}

Based on our hypothesis that voluntariness will be similar between the two study groups, this trial is powered as a non-inferiority RCT. Drawing on data from previous reports validating the questionnaires adapted for this trial [26], we calculate that a sample size of 102 patients (51 in each group) will be needed to assess that the intervention group is non-inferior to the control group with 80% power (alpha = 0.05), with respect to the main outcome defined as the average questionnaire score (continuous measure ranging from 1 to 4), using a two-sample equal-variance *t*-test. We assumed a non-inferiority margin of − 0.3 and a common standard deviation of 0.6 (assumed to be a 5th of the average score range). In order to account for the assumed at most 10% of patients who would decline to participate in this Feedback Session, having not enrolled in the Dummy Trial, the randomization sample size will be 114 patients (57 in each group). The sample size was computed using PASS 2023, version 23.0.2.

### Recruitment {15}

Recruitment will account for the possibility of study drop-out, as described above, and will follow identical protocols to those commonly used for peri-operative trials in our center (using the AADDCToR Trial recruitment model as a template).

## Assignment of interventions: allocation

### Sequence generation {16a}

At the time of their PAC visit, all study-eligible patients will be randomized to one of two groups by a computer-generated sequence. This will be done using a 1:1 block-randomized with varying block sizes (from 2 to 6).

### Concealment mechanism {16b}

Study participants will not be aware of their group allocation, which will be securely cataloged in a REDCap database, until after data lock. Randomization will be performed within REDCap using a program to pull numbers from the computer-generated sequence and assign them to patients at the time of recruitment; there is therefore no human involvement, and the process is fully concealed from both prospective participants and (until the study arm is assigned) prospective investigators. Further concealment measures include trial pre-registration with an embargo so that eligible participants are not able to prematurely unblind themselves to the true nature of the study. Balancing this with the transparency afforded by protocol publication, this protocol was submitted for publication shortly before participant recruitment began to afford a maximum lead time before records of the Consent Study would be made publicly accessible. Data will be provided by these blinded participants through the questionnaire, rather than collected by study personnel.

